#### CAU group

Participants in the CAU group will not receive treatment or support by the researchers. However, they are free to seek any other help they desire, including pharmacological and psychological treatments. All concurrently used treatments will be measured repeatedly by self-reports. Participants in the CAU group will receive access to the intervention after the last follow-up assessment, 12 months after baseline assessment.

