### Sample size

The sample size is conservatively based on the expected difference between the intervention and the care-as-usual group on the primary outcome variable (i.e., depressive symptoms measured with the PHQ-9). Although the intervention evaluated in this study also includes guidance for some of the participants, the between-group effect size estimate is based on meta-analytic evidence for the effect observed in unguided psychological interventions (*d* = 0.28)
[22]. Because treatments effects in a sample with mild to moderately depressed participants could even be lower, we conservatively reduced the estimated effect size to *d* = 0.23. Based on this effect size, a power of 0.80, and an alpha level of 0.05, we would need 300 subjects in each condition. Sample size was further estimated based on a drop-out rate of 40%. Drop-out rates in previous studies of the intervention used in this study range from 9%
[33] to 45%
[32], thus this estimate is rather conservative. Previous research shows that drop-out rates are lower in the control group
[14]. Based on this assumption, we will need a total of 1000 subjects. The sample size was calculated using G-Power
[57]. Based on prior experience of users of the intervention, we expect a non-eligible rate of 70% and may therefore have to screen 3333 participants.

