### Statistical analysis

A statistical plan will be developed and put down in writing prior to the analysis of the data. The main analyses will be conducted on the intention-to-treat sample. A linear mixed-model repeated measures ANOVA with time (T1-T2-T3-T4) as a within groups factor and treatment condition as a between-groups factor will be used for the main research question. Mixed-model repeated measures ANOVA uses all available data of each subject and does not involve the substitution of missing values. Sensitivity analysis will be conducted to analyze the impact of drop-outs on our results. Secondary analyses of the primary endpoint will include a per-protocol approach. Per-protocol analysis will be based on full data-sets of participants who used at least two sessions of the online-based psychological intervention for a complete duration of at least 60 minutes. The analysis of time to onset of a depressive episode and time to remission of depressive episode will be analyzed using survival analysis techniques. The time to onset of depressive episode will be based on monthly PHQ-9 assessments (these allow the assessment of a probable presence or absence of a depressive episode
[26]) and retrospective assessment of the onset of MDE during the final telephone interview (T4). Significance testing of dichotomous data such as diagnostic status will be conducted with chi-square tests. Calculations of within- and between-groups effect sizes (Cohen’s d) will be based on the pooled standard deviations. Regression analyses will be used to identify predictors of treatment outcome. To analyse the use of health-care resources descriptive methods such as absolute and relative frequency scales, measures of dispersion or measures of central tendency will be used. In order to investigate differences between various patient subgroups appropriate statistical tests will be applied. The assortment of the test will depend on the character of the routine administrative data. All analyses will be performed with SPSS statistics, Excel and Visual Basic for Applications (VBA).

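### The per-protocol set selects on programme use, which only the intervention arm can meet, and on complete data, so it gives no randomised comparison and may be biased, probably towards benefit

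*Protocol article*

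**What the plan says.** All references are to the protocol article.

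- **Main analysis (Statistical analysis).** "The main analyses will be conducted on the intention-to-treat sample". The repeated-measures mixed model "uses all available data of each subject and does not involve the substitution of missing values".
- **Per-protocol analysis (same section).** "Secondary analyses of the primary endpoint will include a per-protocol approach". The set has two conditions, one on data and one on use: "Per-protocol analysis will be based on full data-sets of participants who used at least two sessions of the online-based psychological intervention". In full, the use condition covers those "who used at least two sessions of the online-based psychological intervention for a complete duration of at least 60 minutes". No separate rule is given for the control arm.
- **Access to the programme (CAU group).** "Participants in the CAU group will receive access to the intervention after the last follow-up assessment, 12 months after baseline assessment".
- **Drop-out (Sample size).** The plan allows for 40% drop-out, cites 9% to 45% from earlier studies of this programme, and adds: "Previous research shows that drop-out rates are lower in the control group".

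**The concern.** The use condition is measured after randomisation and can be met in one arm only. Taken at its word, the set holds intervention participants alone and supports no comparison with CAU. If controls are added, the intervention arm has lost its low users while their counterparts in CAU, who cannot be identified, remain. People who persist with a self-help programme may differ in prognosis from those who do not, so the two groups need not be comparable even if the programme does nothing.

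The complete-data condition adds a second selection. The main analysis avoids it by using all available observations. Because the protocol cites lower drop-out in controls, this selection may also act unequally on the two arms.

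What is at stake is interpretation. A per-protocol estimate is easily read as the effect of actually using the programme, and the Discussion expects the results to influence policy. The definition sets a session threshold, a time threshold and a data rule, so an analysis plan that follows it would inherit the problem.

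**Working it through.** **1. The plan's own figure.** The per-protocol set has no stated figure, so the only one to reproduce is the sample size. With d = 0.23, power 0.80 and two-sided alpha 0.05, n per arm = 2 x ((1.960 + 0.842)/0.23)^2 = 297 (298 by the exact t-test), against 300 stated. Then 600/(1 - 0.40) = 1000. Both agree, so 0.23 SD and 300 per arm serve as the yardstick below.

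**2. The two rules side by side.** Membership needs two sessions and 60 minutes of use. CAU access begins after the 12-month assessment. Hence no control can qualify during the trial.

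**3. Bias if controls are included and not selected on use.** Let p be the share of the intervention arm meeting the use rule, and g the gap in outcome (SD units) between those who meet it and those who do not, with no treatment effect. The retained group then exceeds the full arm by

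bias = (1 - p) x g.

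Taking 300p users against 300 controls, SE = sqrt(1/(300p) + 1/300). The chance of a nominally significant result at two-sided 5% follows from bias/SE.

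The document gives neither p nor g, so both are assumed. For the outer values of p, the cited drop-out range of 9% to 45% is used as a rough proxy (p = 0.91 to 0.55). Drop-out is not the same as low use.

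| p | g | bias (SD) | share of 0.23 | SE | type I error |
|---|---|---|---|---|---|
| 0.91 | 0.2 | 0.018 | 8% | 0.084 | 5.5% |
| 0.91 | 0.3 | 0.027 | 12% | 0.084 | 6.2% |
| 0.70 | 0.2 | 0.06 | 26% | 0.090 | 10.2% |
| 0.70 | 0.3 | 0.09 | 39% | 0.090 | 17.0% |
| 0.60 | 0.3 | 0.12 | 52% | 0.094 | 24.7% |
| 0.60 | 0.4 | 0.16 | 70% | 0.094 | 39.6% |
| 0.55 | 0.4 | 0.18 | 78% | 0.097 | 45.9% |
| 0.70 | -0.2 | -0.06 | -26% | 0.090 | 10.2% (wrong direction) |

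**4. Bias if controls are also restricted to complete data.** A second model treats being retained as a threshold on a normal variable whose correlation with good outcome is r, the same in both arms. With no treatment effect,

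bias = r x [phi(c_i)/p_i - phi(c_c)/p_c],

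where p_i and p_c are the shares retained in each arm, c the matching normal cut-offs and phi the normal density. At 60% retained the ratio phi/p is 0.644; at 80% it is 0.350. Retention of 60% in the intervention arm is borrowed from the 40% drop-out allowance; r and the control figures are assumed.

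| Controls retained | r = 0.1 | r = 0.2 | r = 0.3 | r = -0.2 |
|---|---|---|---|---|
| 100% | 0.06 | 0.13 | 0.19 | -0.13 |
| 80% | 0.03 | 0.06 | 0.09 | -0.06 |
| 60% | 0 | 0 | 0 | 0 |

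Applying the data rule to controls as well shrinks the bias. It vanishes only if both retention and its link with outcome are equal in the two arms.

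**The case against.** **Controls need not be unselected.** A reader might infer that selected users are compared with an untouched control arm. The document does not say so. The complete-data condition would naturally apply to CAU too, which makes the controls completers, and step 4 shows that this reduces the bias. This stands: the most that can be said is that controls are not selected on use.

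**The direction is not established.** It is tempting to say the analysis is biased towards benefit. The document gives no prognostic gap, and the Intervention section lets participants work at their own pace, so people who improve early may stop. The sign would then reverse. This also stands; benefit is the more plausible direction, no more.

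**The size may be negligible.** Two sessions and 60 minutes is a low bar in a programme of 12 modules counting introduction and summary. At 91% adherence the bias is only about 0.02 to 0.03 SD for gaps of 0.2 to 0.3. Step 3 also ignores baseline PHQ-9, which would absorb part of any gap already visible at T1. Both are fair, and they are why a range is given.

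**The role is limited.** The analysis is secondary, and the wording does not make it the only one: a drop-out sensitivity analysis, predictor regressions and several subgroup analyses are also planned. Nothing says it would override intention-to-treat. That limits the consequence but does not repair the definition, and the drop-out sensitivity analysis is not described as covering selection by use.

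**A rule for controls could be left to the analysis plan.** A written plan is promised before analysis. But the article already fixes a rule that no control can meet. Adding a control group later would not restore randomisation while use is required in one arm only.

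**Conclusion.** The point holds in limited form. The per-protocol set either has no controls or conditions on post-randomisation use in one arm, with complete-case selection on top that may differ by arm. It does not give a randomised comparison and may be biased, probably towards benefit.

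Under the assumed values in step 3 (p from 0.55 to 0.91, g from 0.2 to 0.4), the spurious effect is about 0.02 to 0.18 SD, that is 8% to 78% of the planned 0.23. It turns negative if g is negative. Size and sign rest on quantities the document does not report. The intention-to-treat conclusion is not at risk, so this is something that should be changed rather than a threat to the trial.

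**What to change.** Estimate the effect of use as a complier-average causal effect. Use randomised arm as the instrument and define a complier as someone with at least two sessions and 60 minutes in the programme log. Adjust for T1 PHQ-9 and severity stratum, and include all randomised participants rather than complete cases.

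State the exclusion restriction as an assumption: being offered the programme has no effect on those who do not reach the use threshold. It is weaker in the guided stratum, where supporters e-mail participants every week whatever their use. Repeating the estimate with any log-in as the complier definition is a useful sensitivity analysis but does not verify that assumption.

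If the per-protocol set is kept, state which controls it includes, label it descriptive and non-randomised, and draw no causal conclusion from the difference between arms.

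The cost is a little more analysis work, on usage data that the 60-minute rule already requires, and a wider interval. As a rough guide with 300 per arm and p = 0.7, the standard error is about sqrt(2/300)/0.7 = 0.117 SD, against 0.090 for the per-protocol comparison.

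### Diagnostic status is given an unadjusted chi-square test although the severity stratum and the T1 MINI diagnosis are on record: valid, but inefficient, and without use of drop-outs' partial data

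*Protocol article*

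**What the plan says.** All references are to the Protocol article.

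- **Test.** Statistical analysis: "Significance testing of dichotomous data such as diagnostic status will be conducted with chi-square tests". No stratification factor, baseline covariate or analysis set is attached to this sentence.
- **Role.** Diagnostic status by MINI is listed under Secondary outcomes.
- **Baseline information.** Randomization stratifies by PHQ-9 severity (5–9 v 10–14). The MINI section assesses a current depressive episode or dysthymia. Neither appears among the main exclusion criteria, and the Discussion plans a subgroup analysis by the presence of an episode at baseline, so both kinds of participant are expected in the trial.
- **Contrast with the primary outcome.** For the PHQ-9 model: "Mixed-model repeated measures ANOVA uses all available data of each subject and does not involve the substitution of missing values". That statement does not extend to the binary outcomes.
- **General provisions.** "The main analyses will be conducted on the intention-to-treat sample"; "Sensitivity analysis will be conducted to analyze the impact of drop-outs on our results"; "A statistical plan will be developed and put down in writing prior to the analysis of the data".
- **Expected loss.** Sample size allows for 40% drop-out overall and adds: "Previous research shows that drop-out rates are lower in the control group". No rates by arm are given.

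**The concern.** The protocol names the method here, so this is a choice that can be assessed and not a detail left open. A two-by-two chi-square test of condition against diagnosis cannot carry the stratification factor or the baseline diagnosis. A later positive MINI will mix episodes that were already present at T1 with new ones, so the T1 diagnosis should be strongly prognostic. Leaving it out discards precision that the trial has already paid for.

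The second issue is incomplete follow-up. The mixed model uses whatever PHQ-9 scores a participant has provided. A chi-square test needs a diagnosis for everyone it counts and takes nothing from the other scores of someone who misses the interview. With 40% drop-out planned for, and less of it expected in the control arm, the result could be distorted if people in an episode leave at different rates in the two arms. What is at stake is a secondary outcome, but one that bears on the stated aim of preventing depressive episodes.

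**Working it through.** **1. The plan's own figure.** No sample size is given for diagnostic status; the stated figures concern the PHQ-9. With d = 0.23, power 0.80 and two-sided alpha 0.05: n = 2(1.960 + 0.842)²/0.23² = 297 per arm (298 with the exact t distribution), against the stated 300. Then 600/(1 − 0.40) = 1000. The plan's figures reproduce.

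**2. Cost of leaving out stratum and T1 diagnosis.** The protocol gives no episode rates, so these inputs are assumptions. There are 300 per arm, and four baseline groups:

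| Severity / T1 diagnosis | Share | Risk, control | Risk at odds ratio 0.6 |
|---|---|---|---|
| mild / no | 0.35 | 0.08 | 0.050 |
| mild / yes | 0.10 | 0.30 | 0.205 |
| moderate / no | 0.30 | 0.20 | 0.130 |
| moderate / yes | 0.25 | 0.50 | 0.375 |

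The overall risks are the share-weighted sums, 0.243 and 0.171, a difference of 0.072. The pooled risk is 0.207 and the null standard error is √(2 × 0.207 × 0.793/300) = 0.0331, so z = 2.19. The approximate power of the plain test is Φ(2.19 − 1.96) = 0.59.

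Simulation with 20,000 runs, randomisation balanced on severity, comparing the plain chi-square with a Cochran-Mantel-Haenszel test by severity × T1 diagnosis (standing in for an adjusted analysis):

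| | Plain | Stratified |
|---|---|---|
| Type I error | 0.043 | 0.049 |
| Power, odds ratio 0.6 | 0.60 | 0.66 |

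A second simulation under assumed risks gave 0.58 v 0.64. The loss is about 6 points of power, with no inflation of type I error. In terms of sample size, ((1.96 + 0.404)/(1.96 + 0.248))² = 1.15, so adjustment is worth roughly 15% more participants under these assumptions.

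**3. What drop-out could do if only observed diagnoses were tested.** Assumptions: 500 randomised per arm, no true effect, true rate p = 0.25 in both arms, drop-out 45% (intervention) v 35% (control), leaving 275 v 325. Let q be the drop-out probability without an episode and q′ with one, linked by an odds ratio and by p·q′ + (1 − p)·q = overall drop-out. The observed rate is p(1 − q′)/(1 − overall drop-out). The probability of rejection is from the two-proportion z test.

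Worked case, odds ratio 1.5 in the intervention arm only: q = 0.425, q′ = 0.526, observed rate 0.25 × 0.474/0.55 = 0.216 v 0.250. The difference is −0.034, with null and alternative standard errors 0.0347 and 0.0345. Rejection ≈ Φ((−1.96 × 0.0347 + 0.0344)/0.0345) = 0.17.

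| Dependence of drop-out on episode | Observed rates | Rejection |
|---|---|---|
| none | 25.0% v 25.0% | 5% |
| odds ratio 1.5, intervention only | 21.6% v 25.0% | 17% |
| odds ratio 2, intervention only | 19.2% v 25.0% | 40% |
| odds ratio 1.5, both arms | difference 0.7 points | 5.5% |
| odds ratio 2, both arms | difference 1.1 points | 6.4% |

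With a wider split (50% v 30%) and true rates of 10% to 30%: drop-out unrelated to outcome still gives difference 0 and rejection 5%; odds ratio 2 in both arms gives 1.0 to 2.6 points and 7% to 11%; odds ratio 2 in the intervention arm only gives 3.0 to 7.2 points and 25% to 50%. With equal 40% drop-out and the same dependence in both arms, the difference is 0.

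**4. When the diagnosis is taken.** The text of Assessments places the telephone interviews at T1, T2 and T3. Table 1 marks HRSD, QIDS and MINI at T1, T2 and T4. The MINI section describes T4 as the follow-up interview, and Statistical analysis refers to a final telephone interview at T4. The visits to which the test applies are therefore not settled.

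**The case against.** A reader might infer that the test will be run on observed cases only and so breaks intention-to-treat. The document does not say so. The sentence names no analysis set, and a chi-square test can be applied to imputed diagnoses. The main analyses are placed on the intention-to-treat sample, the drop-out sensitivity analysis is not restricted to the PHQ-9, and a written statistical plan, not shown, is announced. How missing diagnoses are handled is commonly left to such a plan, so its absence from a condensed article is no fault. This objection stands.

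A reader might also infer that omitting the stratum and T1 diagnosis, or unequal drop-out alone, biases the comparison. Neither does: the first costs precision only, and the second gives a difference of 0 when drop-out is unrelated to outcome. The large rejection rates in step 3 need the episode to drive drop-out in the intervention arm alone, and nothing in the document supports that. The 40% is an overall planning value, neither a ceiling nor a difference between arms; the earlier studies cited reach 45%.

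Finally, time to onset and time to remission of an episode are to be analysed by survival methods, which can accommodate incomplete follow-up. So the chi-square is not the only analysis of episodes. That lowers the stakes but does not replace the comparison of diagnostic status itself.

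What remains is that the named test is unadjusted, and that it does not itself draw on partial data as the mixed model does.

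**Conclusion.** The point holds as one of efficiency, with a conditional caution about drop-out. The test is valid for a randomised comparison and slightly conservative under the assumed risks. It loses about 6 points of power (0.58–0.60 v 0.64–0.66) against an analysis using information already collected. That size rests on assumed baseline shares, risks of 8% to 50% and, in the worked example, an odds ratio of 0.6; it would shrink if the T1 diagnosis and severity predicted later status less strongly.

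Bias is a possibility, not a finding. If only observed diagnoses were tested, plausible effects run from none, through about 1 point with rejection of 5.5% to 6.4% (same dependence in both arms, 45% v 35%), to several points if the dependence is confined to one arm. The document does not support choosing the last case, nor a conclusion that the analysis is not intention-to-treat. As the outcome is secondary, this is a worthwhile, low-cost improvement and no threat to the main result.

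**What to change.** 1. Reconcile the interview time points between the Assessments text, Table 1 and the MINI section, and state at which visits diagnostic status is tested.
2. Make the primary test of diagnostic status a logistic regression on condition, severity stratum, T1 MINI diagnosis and T1 PHQ-9. Report a risk difference with its confidence interval, for example by averaging the model's predicted risks under each condition. Keep the chi-square test as a sensitivity analysis.
3. Within the drop-out sensitivity analysis already planned, add multiple imputation of missing diagnoses, within arm, from observed PHQ-9, HDRS and QIDS scores. HDRS and QIDS come from the same telephone interview as the MINI, so for a missed interview the information will come mainly from earlier interviews and the online PHQ-9. State that imputation corrects only for drop-out explained by observed values.

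The cost is wording and modest analysis work. No new data and no change to sample size or conduct are needed.

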## Discussion

This randomized-controlled multicenter study examines the effectiveness of an online psychological intervention in controlling mild to moderate depressive symptoms and preventing emergence and relapse of depression. It is one of the first large trials examining the impact of online self-help interventions on health economic measures
[58]. We will also gain valuable experiences in implementing an online psychological intervention into routine clinical care.

As a major strength of this study, it has a low-threshold of entry as anyone suffering from depressive symptoms can sign up through the study website without further requirements. We will therefore be able to draw inferences with regard to the effectiveness of online-psychological treatments, i.e. the extent to which the treatment achieves its intended effect in the usual clinical setting
[59]. To this end, we will include patients with other comorbid disorders including substance abuse and dependence, anxiety disorders and personality disorders. Also, acute suicidality will be assessed clinically by trained interviewers rather than based on a more rigid exclusion of all patients who cross a certain threshold on a self-rating. These measures will improve the external validity of our study results as the great majority of patients with depression suffer from at least one comorbid mental disorder (41). This strength of the study may also be regarded as a limitation, as it may result in a relatively heterogeneous group of patients. Another weakness of our design is the liberal acceptance of concomitant treatments in our study, which again will increase the external validity of our findings while possibly reducing internal validity.

In addition to the main analysis described in the methods section, our study will be able to address a number of other important research questions, some of which have not been addressed before. To this end, we will conduct subgroup analyses of the influence of pre-specified baseline characteristics on the main outcome measure
[60] and analyses of secondary outcomes. One subgroup analysis will concern the influence of referral source (medical and psychological services versus other) and primary motivation for study participation (self versus other) on the main outcome as many trials of online-based psychological interventions have been conducted outside routine clinical practice
[22] and the applicability of the results to routine clinical practice has therefore been debated
[61]. Other subgroup analysis will concern the influence of baseline severity
[14], presence of depressive episode at baseline, chronicity
[62], parallel treatment
[24] and attitude to online psychological intervention
[63] on the main outcome.

We also plan to undertake a wide range of additional analyses. Weekly PHQ assessments in the intervention group will allow us to identify meaningful patterns of early change in depression during online treatment that are shared by many individual patients and examine whether these patterns predict outcomes at treatment termination and over the follow-up period as well as drop-out or time patients participate in online treatment
[64,65]. Also we may be able to assess whether e-mail support affects working alliance scores and attitudes towards online psychological interventions. The results of this analysis will be biased by depression severity however as only more severely depressed participants receive e-mail support. Finally, this study will be the first to use the Computer-adaptive test for depression (D-CAT)
[45,46] in a prospective randomized controlled trial and will allow the comparison with more established outcome measures.

The present trial will probably be the largest multicentric study conducted thus far of an online depression treatment in which validated diagnostic interviews and symptom severity measures are used and participants are followed for a full year (without those in the control group receiving the intervention). It is hoped that the study will yield meaningful answers to the question of whether the internet-based intervention studied here can contribute to the effective and efficient prevention and treatment of mild to moderate depression on a population level. The results of this trial are expected to influence policy decisions with regard to whether such interventions ought to be implemented more widely in order to meet the challenge posed by the global depression treatment gap.

